**Sample Size**

Sample size has been calculated under the hypothesis of superiority of intervention versus standard of care assuming a one tailed alfa error of 0.05 and beta error of 0.2. According to the study with Remdesivir by Beigel et al (PMID: 32445440; DOI: 10.1056/NEJMoa2007764), a 42% of patients with basal punctuation of 4 to 6 at day 15 in the WHO ordinal scale recovered. A similar estimation (40%) is made by Rai et al (Rai, S.N., Qian, C., Pan, J. et al. Statistical design of Phase II/III clinical trials for testing therapeutic interventions in COVID-19 patients. BMC Med Res Methodol 20, 220 (2020). https://doi.org/10.1186/s12874-020-01101-z) for patients on intermediate risk (3 to 5 in this same scale). Based on these assumptions the table below shows the sample size for relative risks of 0.7 and 0.65 and recovery percentage of 40%, 45% and 50% in the standard of care group. Therefore, the objective is to recruit 82 patients per arm.

| **RR** | **P1** | **P2** | **SEnvelop** |
| --- | --- | --- | --- |
| 0.7 | 40 | 57.14 | 104 |
| 0.7 | 45 | 64.29 | 82 |
| 0.7 | 50 | 71.43 | 64 |
| 0.65 | 40 | 61.54 | 64 |
| 0.65 | 45 | 69.23 | 50 |
| 0.65 | 50 | 76.92 | 37 |

P1: percentage of recovery in standard of care group;

P2: percentage of recovery in intervention group.

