**Statistical analysis.**

The crude probability of recovery at 14^th^ day will be compared by Chi-Square test. A covariate‐adjusted estimation of the ratio of probability of recovery in experimental treatment to standard of care will be based on the standardization approach of Ge et al. (2011; Ge, M., Durham, L.K., Meyer, R.D., Xie, W. and Thomas, N. (2011) Covariate‐adjusted difference in proportions from clinical trials using logistic regression and weighted risk differences. Drug Information Journal, 45, 481–493). Covariates to be included will be age, sex, basal punctuation in WHO scale at baseline and presence of cardiovascular risk factors.

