# General considerations

Tabular summaries will be presented by treatment group.

Categorical data will be summarized by number and percentages. Continuous variables will be summarized by descriptive statistics. Recover incidence (RI): Time to recovery.

The overall survival rate will be calculated by the nonparametric Kaplan-Meier method. Fisher exact test will be used to identify those patient characteristics that are significantly associated with treatment response (complete or partial).

For quantitative characteristics a chi-squared trend test will be conducted to examine whether the proportion of patients responding to treatment either increased or decreased across the levels of the characteristic.

The results of the statistical analysis will be displayed in the tables and as mean ± SD in the Figures. Levels of significance will be expressed as p-values (*p < 0.05).

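### Phase II is sized for a one-tailed 5% test, but nothing carries that sidedness to the primary chi-square test; read in the usual way, its power at 82 per group is about 70%, not 80%

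*Protocol*

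**What the plan says.** Three places in the protocol bear on this.

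- **Sample Size (Study Population).** The calculation supposes that cells are superior to usual treatment and is made "assuming a one tailed alfa error of 0.05 and beta error of 0.2". The table row adopted is "0.7 | 45 | 64.29 | 82" (planning ratio, recovery on standard of care, recovery on intervention, n), and the text concludes: "Therefore, the objective is to recruit 82 patients per arm".
- **Statistical analysis (directly after Sample Size).** "The crude probability of recovery at 14^th^ day will be compared by Chi-Square test". No alpha, direction or rejection rule is given. A covariate-adjusted "ratio of probability of recovery in experimental treatment to standard of care" is to be estimated as well.
- **General considerations (Data Analysis and Statistical Methods).** "Levels of significance will be expressed as p-values (*p < 0.05"). This is a general line and does not mention the primary comparison.

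The protocol nowhere says that the day-14 comparison is one-sided, that the chi-square is judged at a two-sided 0.10, or that the direction of the difference is checked before success is claimed.

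**The concern.** A Pearson chi-square on a 2×2 table equals the square of the two-proportion z statistic, so it rejects for a difference in either direction. At p < 0.05 it needs |z| > 1.96. The sample size assumes success whenever z > 1.645 in favour of cells. If the analysis is run as an ordinary chi-square at 5%, the 80% power behind the adopted size is not the power of the test performed.

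The decision rule is also open for one band of results. If z lies between 1.645 and 1.96, the trial succeeds by the rule used for sizing and fails by the ordinary reading of the test named. The trial is open label (Study design), so the tail should be fixed in writing before anyone sees outcome data.

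**Working it through.** **Inputs.** From Sample Size: p1 = 0.45, p2 = 0.45/0.7 = 0.6429, alpha 0.05 one-tailed, power 0.80, n = 82. From Statistical analysis: chi-square test. From General considerations: p < 0.05. Equal groups, from Subject Treatment Assignment (1:1). Assumption: chi-square without continuity correction, since none is mentioned.

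**Formula (pooled variance under the null).**

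n per group = [zα·√(2·p̄·q̄) + zβ·√(p1q1 + p2q2)]² / (p2 − p1)²

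- p̄ = 0.5464, so √(2·p̄·q̄) = √0.4957 = 0.7041
- p1q1 + p2q2 = 0.2475 + 0.2296 = 0.4771, square root 0.6907
- p2 − p1 = 0.1929, squared 0.03719
- zβ = 0.8416

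**Step 1: reproduce the plan's 82.** One-sided, zα = 1.645: (1.1581 + 0.5813)² / 0.03719 = 81.3, so 82 per group. This matches the adopted row. The same formula gives 105, 64, 66, 51 and 39 for the other five rows, against 104, 64, 64, 50 and 37 in the table, so the whole table was built one-tailed.

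**Step 2: the same row, two-sided 5%.** zα = 1.960: (1.3799 + 0.5813)² / 0.03719 = 103.4, so 104 per group. The other two-sided methods tried (unpooled, arcsine, log ratio, continuity-corrected) give 101 to 114. None comes near 82.

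**Step 3: power at 82 per group.** Power = Φ([(p2 − p1)·√n − zα·0.7041] / 0.6907), with (p2 − p1)·√82 = 1.7464.

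- One-sided: (1.7464 − 1.1581)/0.6907 = 0.852, power 80.3%
- Two-sided: (1.7464 − 1.3799)/0.6907 = 0.531, power 70.2%

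Exact binomial enumeration of the chi-square gives 80.3% and 70.3%. At the 42% standard-of-care rate that the protocol also cites, with the same planning ratio, the figures are 74.9% and 63.7%.

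**Step 4: type I error at 82 per group, 45% recovery in both groups (exact).** In favour of cells: 0.0496 under the one-sided rule and 0.0248 under the two-sided rule.

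**Step 5: the undecided band.** Suppose 37/82 recover on standard of care and 49/82 on cells. The difference is 12/82 = 0.1463, the pooled rate is 86/164 = 0.5244, and the standard error is √(0.5244·0.4756·2/82) = 0.0780. So z = 1.88 and the chi-square p is 0.061: success at one-sided 0.05, no success at p < 0.05. If the planning effect is true, about 80% − 70% = 10% of trials of this size fall in that band.

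**The case against.** The best defence is that no contradiction is written down. A reader might infer that the protocol specifies a two-sided test; it does not. The words never appear. The p < 0.05 line follows a sentence on how results are displayed, and its asterisk looks like a convention for tables and figures. The only error rate tied to intervention versus standard of care is the one-tailed 0.05. A chi-square can serve that plan through its signed root, and an analysis plan not at hand may say so. This stands as far as it goes: the two-sided reading comes from the nature of the test, not from the text. But the protocol fixes the sizing tail, the test and a threshold, and in their ordinary sense these do not fit together.

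Three stronger readings should also be set aside.

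- **Inflated false positives.** The opposite holds: the error in favour of cells falls from 0.05 to 0.025.
- **Power of about 42% caused by sidedness.** Enrolment is 82 per HLA arm, then randomised 1:1, which leaves 41 per group. Power there is 54% one-sided and 42% two-sided (45% by exact enumeration). Most of that fall from 80% comes from counting 82 per arm instead of per comparison group, which is a separate issue.
- **A reversed effect.** The planning ratio of 0.7 is standard of care over intervention (45/64.29), while the analysis reports experimental over standard of care. A reader might infer that benefit and harm could be confused. The table note defines both percentages, and every row has the higher recovery on intervention, so neither the sample size nor the test changes. It is a labelling point.

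**Conclusion.** The point holds as a mismatch between sizing and stated analysis. Under the ordinary reading of the chi-square at p < 0.05, power at the design alternative is about 70% at 82 per group, not 80%, and the success rule is unclear for z between 1.645 and 1.96. The loss of about 10 percentage points equals a shortfall of 22 patients per group (104 − 82).

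This rests on the protocol's own rates, on 82 per comparison group, and on an uncorrected chi-square. With a continuity correction the exact two-sided power at 82 would be about 65%. If an analysis plan already declares the primary test one-sided at 0.05, the power loss disappears and only the protocol text needs aligning. Because the rule decides whether the primary endpoint is met, it should be settled before any data review.

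**What to change.** State one sidedness in Sample Size, Statistical analysis and General considerations. Either:

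- **(a)** declare the primary day-14 comparison one-sided at 0.05 in favour of cells, using the signed root of the chi-square, and report a matching 90% two-sided confidence interval; or
- **(b)** keep the chi-square at two-sided 0.05 and restate its power as about 70% at 82 per comparison group (about 42–45% if 82 per HLA arm is split into 41 versus 41, to be resolved separately).

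Both are text changes. Option (b) states a less favourable power. Holding 80% under (b) would take 104 per group, which is a change of size and not only of text.

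As an editorial note, express the planning ratio in the direction of the analysis: 1/0.7 = 1.43 and 1/0.65 = 1.54, experimental over standard of care.

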## Sample size:

A total of 182 patients will be included in this clinical trial.

The plan is to enroll 18 patients in the first dose escalation segment (phase I): 9 patients per arm (3 patients in each cohort, for both arms).

A total of 164 patients will be included in the phase II: 82 patients per arm.

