## Subject Treatment Assignment

Patients will be allocated into two groups: Arm A and Arm B depending on HLA typing.

For the phase I, patients on each arm will subsequently undergo a correlative allocation into the different cohorts (1,2,3).

The decision to proceed to each subsequent dose level (next cohort) will be made based on safety and tolerability data from the prior lower dose level. Safety data for at least 7 days post-dose from all the subjects at the prior lower dose will be reviewed before dose escalation.

The next cohort will open if all the patients in the previous cohort have been included and no safety issues have aroused during the follow-up after cell infusion (data of at least 7 days after cell infusion is required to proceed to each subsequent dose). Patients will continue to be followed for possible DLTs during the 21 days following cell infusion.

For phase II, eligible patients will be allocated to arm A or B considering HLA typing and within each arm they will then be randomized in a 1:1 ratio to 1 of 2 treatment groups (SoC or SoC+RP2D).

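### The calculated 82 is the size of each compared group, but the protocol uses it as the size of each HLA arm, so each product's comparison with its own SoC group is 41 v 41 with about 54% power, not 80%

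*Protocol*

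**What the plan says.** The Sample Size paragraph under Study Population (protocol) describes one contrast: "Sample size has been calculated under the hypothesis of superiority of intervention versus standard of care". The error rates behind this calculation are given as follows: "assuming a one tailed alfa error of 0.05 and beta error of 0.2". Its table gives the number required for each pair of recovery rates, with "P1: percentage of recovery in standard of care group" and P2 the corresponding percentage on intervention. The row adopted is "0.7 | 45 | 64.29 | 82", that is RR 0.7, 45% on SoC and 64.29% on intervention. The conclusion is "Therefore, the objective is to recruit 82 patients per arm".

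The Protocol Summary then states: "A total of 164 patients will be included in the phase II: 82 patients per arm". The opening of Study Population and the closing Sample size section under Data Analysis and Statistical Methods repeat these numbers.

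In the design sections an arm is not a treatment group. Patients go to Arm A (memory T cells) or Arm B (NK cells) by HLA typing, and under Subject Treatment Assignment, "within each arm they will then be randomized in a 1:1 ratio to 1 of 2 treatment groups (SoC or SoC+RP2D"). Each arm therefore has its own concurrent SoC group.

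The Statistical analysis paragraph names a chi-square test of recovery at day 14 and an adjusted ratio of recovery probabilities. It does not say whether the arms are analysed separately or together. For the adjusted estimate: "Covariates to be included will be age, sex, basal punctuation in WHO scale at baseline and presence of cardiovascular risk factors".

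**The concern.** The word arm does two jobs. In the sample size table it can only mean one side of the SoC-versus-intervention comparison. In the enrolment figures it means an HLA stratum that contains both sides of that comparison. Carrying 82 from the first use to the second halves the number available for each product.

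At stake is the stated beta of 0.2. If the trial is meant to judge memory T cells and NK cells separately, neither comparison has the power that the protocol claims, and a non-significant result in either arm would be weaker evidence than a reader of the protocol would think. If the trial is meant to judge cell therapy as a whole, the power is as stated, but the protocol does not say that this is the primary test. A reader cannot tell which is intended.

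**Working it through.** **Inputs.** From the Sample Size paragraph: p1 = 0.45, p2 = 0.45/0.7 = 0.6429, one-sided alpha 0.05 (z = 1.645), power 0.80 (z = 0.842). From Subject Treatment Assignment: 1:1 within each arm. From the summary: 82 per arm, 164 in phase II.

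**Step 1. Reproduce the 82.** Two-proportion formula with pooled variance under the null:

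n per group = [1.645 × √(2p̄(1−p̄)) + 0.842 × √(p1(1−p1) + p2(1−p2))]² / (p2−p1)²

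with p̄ = 0.5464 and p2−p1 = 0.1929:

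- first term: 1.645 × 0.7041 = 1.158
- second term: 0.842 × 0.6907 = 0.581
- n = (1.739 / 0.1929)² = 81.3, so 82 **per group**, 164 for the two groups.

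For the six rows this formula gives 105, 82, 64, 66, 51 and 39 per group, against 104, 82, 64, 64, 50 and 37 in the table. The unpooled formula, with P2 rounded to a whole percent in five rows and left at 61.54 in the fourth, gives all six exactly. For the adopted row, two-sided or continuity-corrected versions give 92 to 114 per group. No version tried gives 82 as a two-group total. The table is sound as a list of per-group sizes.

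**Step 2. Apply the protocol's allocation.** 82 per HLA arm at 1:1 gives 82/2 = 41 v 41 for each product.

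**Step 3. Power at each size.** Power = Φ{[(p2−p1)√n − 1.158] / 0.6907}:

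- n = 82: (1.746 − 1.158)/0.6907 = 0.852, power 80.3% (exact enumeration of the uncorrected chi-square: 80.3%).
- n = 41: (1.235 − 1.158)/0.6907 = 0.111, power 54.4% (exact: 54.1%; unpooled formula: 55.7%).

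**Step 4. Sensitivity at 41 v 41, one-sided 0.05.**

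| SoC | Intervention | RR | Power |
| --- | --- | --- | --- |
| 40% | 57.14% | 0.70 | 46.3% |
| 42% | 60.00% | 0.70 | 49.4% |
| 45% | 64.29% | 0.70 | 54.4% |
| 50% | 71.43% | 0.70 | 63.7% |
| 45% | 69.23% | 0.65 | 72.2% |
| 50% | 76.92% | 0.65 | 82.2% (exact 82.5%) |

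The 40% and 42% are the SoC rates that the Sample Size paragraph itself cites.

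**Step 5. Detectable effect.** With 41 v 41 and SoC 45%, 80% power is reached at about 72% on cells: RR = 0.45/0.7175 = 0.63, a gain of about 27 points instead of 19.

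**Step 6. Numbers needed for the stated beta per product.** 82 × 2 groups × 2 arms = 328 in phase II, or 346 with the 18 phase I patients.

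**The case against.** The best defence is that the phase II comparison is pooled. The Sample Size paragraph powers a single contrast, the Statistical analysis paragraph estimates a single ratio of experimental treatment to SoC, and the hypothesis, objective and primary outcome speak of NK or memory T cells together. The 164 patients, split 1:1 within each arm, give exactly 82 v 82. On that reading the planned power is intact and only the word arm is loose.

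This stands as a possible reading, so the documents do not support saying that the trial as a whole has 54% power. It does not remove the problem. No section states the pooling, and the summary uses arm for the HLA strata in the sentence just before, on phase I. The two products also have separately determined doses and separate concurrent SoC groups, so a pooled result would not answer the question for either product.

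Three further inferences are tempting and go too far.

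- That a per-product comparison would be uninformative: at the protocol's own most favourable row (50% v 76.92%), 41 v 41 has 82.5% exact power.
- That the remedy is simply to write 82 per treatment group throughout: that is right only under pooling, and it would remove the only stated size of each HLA arm.
- That the error rate is inflated: the chance of at least one false claim, 1 − 0.95² = 9.75%, applies only if two separate primary tests are run at one-sided 0.05, and the protocol does not say that they are.

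**Conclusion.** The concern holds in this form: 82 is a per-group number applied to arms that each contain two groups, and the stated beta of 0.2 is wrong for each product's comparison with its own SoC group. Power there is about 54%, not 80%, at the protocol's own rates and one-sided 0.05. It is about 49% and 46% at the cited SoC rates of 42% and 40% with RR 0.7. The figures assume equal arms of 82, exact 1:1 allocation, no losses and an uncorrected chi-square.

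The 80% is correct for one comparison only, both products pooled against both SoC groups, and the protocol does not name that as its primary test. A reader might infer either that the trial is underpowered overall or that it must be pooled. The documents settle neither, and choosing between them is a design decision for the sponsor.

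**What to change.** Keep 164 patients as 82 per HLA arm, 41 v 41 within each. In the Sample Size paragraph, state that the tabulated 82 is the number per compared group, and say which comparison is primary.

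- **If it is per product:** restate the power as about 54% at 45% v 64.29%, or the detectable effect as RR about 0.63 at SoC 45%. Note that the stated beta would need 82 per group in each arm, 328 in phase II. If both products are tested as primary, address the 9.75%.
- **If it is pooled:** say so explicitly and claim 80% for the pooled test only. Account for HLA arm in that test, for example with a Cochran-Mantel-Haenszel test stratified by arm, and add arm to the covariates of the adjusted estimate, because randomisation is within arm. This costs little or nothing; any gain depends on how far SoC recovery differs between arms, for which the protocol gives no figures. Report each product's 41 v 41 comparison as secondary, with its true power.

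Under either option, use the same wording in the Protocol Summary, the opening of Study Population and the closing Sample size section. The cost is wording and, under pooling, one changed analysis line. No extra patients are needed unless the sponsor wants the stated power for each product. The stated per-product power becomes less favourable.

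### The phase II sample size of 82 rests on an unexplained 45% control recovery rate; at the relative risk of 0.7 that yields 82, the cited rates of 40% and 42% give about 71% and 75% power, not 80%

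*Protocol*

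**What the plan says.** The calculation is in the Protocol under Study Population, Sample Size. It is a superiority calculation, "assuming a one tailed alfa error of 0.05 and beta error of 0.2". Two published sources are cited for recovery. The first, a remdesivir trial, is reported as "a 42% of patients with basal punctuation of 4 to 6 at day 15 in the WHO ordinal scale recovered". For the second, a paper on COVID-19 trial design, the text says "A similar estimation (40%) is made by", here for patients at intermediate risk.

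The paragraph then says that these assumptions underlie a table covering "relative risks of 0.7 and 0.65 and recovery percentage of 40%, 45% and 50% in the standard of care group", and concludes "Therefore, the objective is to recruit 82 patients per arm". Two rows matter most:

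- "0.7 | 45 | 64.29 | 82" (relative risk, control %, intervention %, n), the only row that gives 82;
- "0.7 | 40 | 57.14 | 104", the row with the same relative risk at the cited 40%.

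No row uses 42%. The text does not say which relative risk or which control rate is adopted. The summary gives the total: "A total of 164 patients will be included in the phase II: 82 patients per arm". Subject Treatment Assignment says that patients are placed in Arm A or B by HLA typing and then randomised 1:1 within each arm to standard of care with or without cells.

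**The concern.** The conclusion is presented as following from the cited rates, but it comes from a row whose control rate is higher than both of them. At relative risk 0.7 a higher control rate needs fewer patients, because the implied absolute difference grows: 17.1 points at 40%, 18.0 at 42% and 19.3 at 45%. Moving from 40% to 45% lowers the table's requirement from 104 to 82.

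At stake is the meaning of the stated beta of 0.2. Someone interpreting a null result would take 80% power as supported by the two sources, when it is supported only at a rate for which the Protocol gives no basis.

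**Working it through.** **Inputs.** One-sided alpha 0.05 (z = 1.645), power 0.80 (z = 0.842), P1 = control recovery, P2 = P1/RR, equal groups. All come from the Sample Size paragraph and its table; the table's P2 values confirm P2 = P1/RR (45/0.7 = 64.29). The planned test is chi-square, so I use the pooled-variance normal approximation without continuity correction.

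**Formulas.** Let d = P2 − P1, p̄ = (P1 + P2)/2, s0 = √[2p̄(1 − p̄)] and s1 = √[P1(1 − P1) + P2(1 − P2)].

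- n per compared group = (1.645·s0 + 0.842·s1)² / d²
- power at m per group = Φ[(d·√m − 1.645·s0) / s1]

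**Step 1: reproduce 82.** For 45% v 64.29%: d = 0.1929, s0 = 0.7041, s1 = 0.6907, so n = 81.3, rounded up to 82. Power at 82 is Φ[(1.746 − 1.158)/0.6907] = Φ(0.852) = 80.3%. The remaining rows, in the table's order, come to 105, 64, 66, 51 and 39 against the printed 104, 64, 64, 50 and 37, so all are within 2. The formula returns patients per compared group.

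**Step 2: the cited rates at RR 0.7, 82 per compared group.**

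- 40% v 57.14%: d = 0.1714, s0 = 0.7068, s1 = 0.6963. n = 104.05, that is 105 rounded up (the Protocol prints 104). Power at 82 = Φ[(1.552 − 1.163)/0.6963] = Φ(0.560) = 71.2%.
- 42% v 60%: d = 0.18, s0 = 0.7070, s1 = 0.6954. n = 94.3, that is 95. Power at 82 = Φ[(1.630 − 1.163)/0.6954] = Φ(0.672) = 74.9%.

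**Step 3: the other tabulated effect size, and the size actually randomised.** The same formula gives:

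| RR | Control rate | Intervention rate | Power, 82 per group | Power, 41 per group |
| --- | --- | --- | --- | --- |
| 0.7 | 40% | 57.1% | 71.2% | 46.3% |
| 0.7 | 42% | 60.0% | 74.9% | 49.4% |
| 0.7 | 45% | 64.3% | 80.3% | 54.4% |
| 0.65 | 40% | 61.5% | 87.3% | 62.3% |
| 0.65 | 42% | 64.6% | 90.2% | 66.2% |

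The last column applies if each HLA arm is compared with its own standard-of-care group: 164 / 2 arms = 82, and 82 / 2 treatment groups = 41.

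**Step 4: hold the absolute difference instead.** If the 19.3-point difference of the 45% row is kept, power at 82 per group is 80.0% at both 40% v 59.3% and 42% v 61.3%. These pairs correspond to relative risks of about 0.675 and 0.685.

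**The case against.** The best defence is that the table is an open sensitivity grid and the sponsor took its middle control rate. The 104 for 40% is printed in the same table, so nothing is hidden. The cited rates are background, not declared design values: both sources group patients by the WHO ordinal scale, whereas the Phase II primary outcome is normalised temperature and oxygen saturation sustained for 24 hours, or recovery from lymphopenia, through day 14. The lymphopenia route can only add responders to the fever-and-saturation criterion, so a rate above 42% is conceivable. Step 4 also shows that at both cited rates 82 per group reaches 80% power for a relative risk between the two tabulated values.

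Much of this stands. It rules out three stronger readings that a reader might infer:

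- **That 82 is a calculation error.** It is not; it reproduces exactly for its row.
- **That 80% power fails at the cited rates whatever the effect.** It does not. At 0.65 the table itself asks for only 64 at 40%, and 82 per group exceeds 80% at both rates.
- **That 40% to 42% is the right control rate for this trial.** The documents do not show this. The endpoint differs, and the true rate could lie on either side.

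What the defence does not supply is a reason for 45%. The Protocol does not make the endpoint argument. The grid is not centred on the sources: 40% is its lowest value, and 42% lies below its midpoint. The effect is specified as a relative risk, and none of the 0.65 rows gives 82.

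**Conclusion.** The point holds as an unsupported planning assumption, conditional on relative risk 0.7, the only tabulated effect size that yields 82. On that basis, with a one-sided 5% test and 82 per compared group, power is about 9 points below the stated 80% at 40% control recovery and about 5 points below at 42%. The requirement at the cited rates is 104 (Protocol table) and about 95 per group.

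The lower figures of 46%, 49% and 54% answer a different question, whether 82 is the size of an HLA arm or of a randomised group. They should not be used to enlarge this point: the gap between the cited rates and the chosen row is there even if 82 is per group. They matter here because any restated power has to refer to the number really compared. Only pooling the two HLA arms would give 82 against 82.

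**What to change.** Revise the Sample Size paragraph in three respects:

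1. State which relative risk and which control recovery rate are adopted.
2. Either justify 45% for this trial's own day-14 recovery endpoint, or restate the power at 40% and 42%. At relative risk 0.7 and 82 per compared group, that is about 71% and 75%; the 0.65 results of 87% and 90% can be given beside them.
3. Give the power for the number actually randomised per compared group. If each HLA arm is analysed separately with 41 per group, that is about 46%, 49% and 54% at control rates of 40%, 42% and 45% (relative risk 0.7).

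The cost is rewording one paragraph. Enrolment, treatment and conduct do not change. The downside is a less favourable stated power.
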